#### Treatment assignment and sample size rationale

Families will be assigned on a 1:1 basis to MFG alone (*n* = 40) or MFG plus My MFG (*n* = 40) (see Fig. 2 CONSORT flowchart) via predetermined sequence based on random permutation calculation by the project director, who is blind to family information. Both treatment conditions will run in parallel within each participating clinic. Sample size will be determined based on previous randomized controlled trial data suggesting that a sample size of 40 participants per condition would provide a meaningful difference in homework completion between those that are typically highly engaged and those that are less engaged.

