### Interventions

#### Multiple family group

Multiple family group (MFG) is a 16-week service delivery strategy that was guided by a manualized protocol. Each group included six to eight families, composed of identified youth, their adult caregiver(s), and sibling(s) between the ages of 6 and 18. As a foundation, MFG takes a common elements approach by identifying essential components from the empirical literature regarding core effective practices for treating DBDs, represented as the 4Rs (i.e., rules; responsibility; relationships; respectful communication) and factors related to family engagement in mental health services, represented as 2Ss (stress and social support. Each of the 16 sessions that focused on one of the 4Rs and 2Ss and proceeded with the following processes: (a) creating social networks; (b) information exchange/homework review; (c) group discussion regarding the skill; (d) individual family practice; and (e) homework assignment.

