#### Measures

Data will be collected at baseline, pretreatment, at each session, and at post-treatment. See Table 1 for the data collection tools and timing of the collection of each measure. My MFG usage data (e.g., frequency, duration of use, which components used, etc.) will also be collected directly from servers throughout treatment.

**Table 1 Tab1:** Outcome measures for pilot randomised controlled trial phase

Domain	Measure	Reporter	Time of assessment
Homework process; homework quantity and quality	Homework rating scale-II [9]	Parent and clinician	Every session
Homework process	Homework adherence and competence scales [9]	Independent observer	Every session
Attendance	Session attendance	Clinician	Every session
Consumer satisfaction and feedback	Treatment attitude inventory [40] Feedback questionnaire Group and individual consultancy meeting	Parent; target child; therapist	Postreatment

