#### Primary and secondary aims

The primary aim will be to obtain summary statistics of the key outcomes (quality of the design, do, and review phases, quality of homework completed), to determine usage of the My MFG application, and to identify challenges and barriers for uptake of My MFG application. An additional primary aim will be to determine the feasibility of the study protocol. Secondary analyses will compare MFG-alone to MFG plus My MFG on key homework process outcomes. The following hypothesis for this phase includesGreater quality of the “design” and “do” process rated by clinicians, parents, and independent coders. As My MFG is being developed to specifically address the design and do process, we hypothesize that clinicians, parents, and independent coders will rate the quality of these two processes to be high. We also hypothesize that MFG plus My MFG, compared to MFG-alone, will result in significantly better design and do process outcomes.Greater quantity and quality of homework assignments rated by clinicians and parents. Given aim #1 and hypothesis #1, we hypothesize that the quantity and quality of homework completed will be high for the MFG plus My MFG group. We also hypothesize that MFG plus My MFG, compared to MFG-alone, will result in significantly better scores on homework adherence and quality measures.Greater quality of the “review” process as rated by clinicians, parents, and independent coders. Given aim #2 and hypothesis # 2, we hypothesize that the review process during the MFG plus My MFG condition will be rated high by families (based on improved adherence to and quality of homework completed) as review of homework requires that homework be completed in a high-quality manner. Low rates and quality of homework limits opportunities for effective review. We also hypothesize that MFG plus My MFG, compared to MFG-alone, will result in significantly better scores on the review process.Greater satisfaction with treatment as rated by the parent, target child, and clinicians. We hypothesize that families and clinicians in the MFG plus My MFG condition will have high levels of satisfaction with the treatment process, given that the goal of My MFG is to enhance autonomous motivation, competency, and relatedness while enhancing the process of homework during MFG. We also hypothesize that MFG plus My MFG, compared to MFG-alone, will result in significantly higher satisfaction with treatment.

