Secondary analyses will focus on between group (group: MFG plus My MFG and MFG-alone) X 2 (time: pre-treatment and post-treatment) repeated measures multivariate analysis of variance (MANOVA) to address homework quantity and quality at each session, average homework quantity and quality across all sessions, and quality of the design, do, and review processes. Alpha-inflation correction procedures will not be used for subsequent contrasts given the exploratory nature of the study. Follow-up analyses will include calculation of effect size by subtracting the MFG plus My MFG group mean from the MFG-alone group mean and dividing by the pooled standard deviation of the groups. Effect size data will be an important indicator of a “signal” that My MFG may be improving the homework process given the relatively small sample size of this study. Independent sample *t* tests will be used for determining differences between treatment conditions on consumer satisfaction to treatment. It is important to state that the results of these secondary analyses will be treated with caution given the small sample size of the RCT.

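### The pre/post MANOVA named for homework ratings from 16 sessions would, if run on the session series, analyse only families with complete ratings; a mixed model on all available ratings, plus a whole-programme homework count, avoids this

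*Protocol article*

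**What the plan says.** Under Data analyses, the protocol article sets the secondary comparison as group "X 2 (time: pre-treatment and post-treatment) repeated measures multivariate analysis of variance (MANOVA"). It applies this to "homework quantity and quality at each session, average homework quantity and quality across all sessions, and quality of the design, do, and review processes".

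The Measures section states: "Data will be collected at baseline, pretreatment, at each session, and at post-treatment". Its Table 1 has homework quantity and quality rated at every session, with the reporter given as "Parent and clinician". An independent observer also scores the homework process at every session, and attendance is recorded. The programme length comes from the Multiple family group section: "Each of the 16 sessions that focused on one of the 4Rs and 2Ss".

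Forty families are allocated to each arm. The feasibility aims set retention at 80% of the sample. The primary analyses are descriptive because the trial is acknowledged to be underpowered. The article asks for care in reading the secondary results, and the only reason it gives is the small sample. It also gives the between-arm effect size an important role as the signal that the app may help.

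**The concern.** Standard MANOVA needs a complete response vector for each unit. The outcomes here are spread over 16 sessions, the retention target allows for losses, and the time factor has only two levels. The named model therefore does not match the data, and the most literal way of forcing the session data into it is a complete-case analysis.

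Two separate things are at stake:

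- **Loss of families.** With one vector of session ratings, a single missing rating removes a family. The families left are the regular attenders, who may also be the better homework completers.
- **A benefit that does not register.** With per-session tests or averages over rated sessions, most families stay in. If ratings are missing when families are absent, however, the result describes homework given attendance. An app meant to raise motivation could act partly by keeping families coming, and that part would be left out. The article itself links later ratings to earlier behaviour: "Low rates and quality of homework limits opportunities for effective review".

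Both affect the effect size that is meant to inform a larger trial.

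**Working it through.** **The plan's own figures.** 40 + 40 = 80 families; 80% retention gives 0.80 × 80 = 64. The 80% is a target for study retention, not a session attendance rate. The article gives no attendance rate, so every attendance figure below is an assumption.

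**1. Complete families if all 16 sessions form one vector.** With attendance probability p per session and independent misses, the expected number complete is 80 × p^16:

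| p | p^16 | of 80 |
|---|---|---|
| 0.99 | 0.851 | 68 |
| 0.98 | 0.724 | 58 |
| 0.95 | 0.440 | 35 |
| 0.90 | 0.185 | 15 |
| 0.80 | 0.028 | 2 |

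Independence is the harshest case. If p varies between families as a beta distribution, the number is 80 × E[p^16]:

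| mean p | beta precision | complete fraction | of 80 |
|---|---|---|---|
| 0.95 | 5 | 0.681 | 55 |
| 0.90 | 5 | 0.459 | 37 |
| 0.90 | 2 | 0.606 | 49 |
| 0.80 | 5 | 0.200 | 16 |

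**2. Can the model then be fitted?** Quantity and quality over 16 sessions make 2 × 16 = 32 variables. With two groups, error degrees of freedom are the number of families minus 2. Fifteen families give 13, fewer than 32, so the multivariate test cannot be computed. With 37 to 49 families there are 35 to 47, only just enough.

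**3. Who is left?** A simulation assumed a correlation of 0.6 between attendance propensity and homework level. Complete cases had a mean homework level 0.31 to 0.37 SD above the full sample at 90% attendance, and 0.56 SD above it at 80%. One average per family kept at least 99.9% of families and moved the mean by less than 0.01 SD. That simulation let homework level be the same in attended and missed weeks. If families miss the weeks in which they did no homework, the averages would be too high by an amount the article does not allow one to compute.

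**4. What averages over rated sessions leave out.** Constructed inputs: 60% engaged families attend 90% of sessions and complete 70% of homework when present. The other 40% complete 30% when present and attend 40% of sessions under MFG alone, 70% with the app. Ratings exist only for attended sessions, and a missed session counts as no homework.

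- Mean of family averages, both arms: 0.6 × 0.7 + 0.4 × 0.3 = 0.54.
- Homework done per scheduled session, MFG alone: 0.6 × 0.9 × 0.7 + 0.4 × 0.4 × 0.3 = 0.378 + 0.048 = 0.426.
- Homework done per scheduled session, with app: 0.378 + 0.4 × 0.7 × 0.3 = 0.378 + 0.084 = 0.462.

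Over 16 sessions this is 16 × 0.426 = 6.8 against 16 × 0.462 = 7.4 assignments per family. The family averages show no difference.

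**The case against.** The strongest reply is that the article never says families with a missed session are dropped. Its time factor has two levels, so it defines neither a 16-session vector nor a 32-variable model. Homework at each session can be read as separate analyses, each losing only that session's absentees. This stands: the collapse in step 1 is conditional on one reading.

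It also stands that the text does not confine ratings to attended sessions. Clinicians rate homework too, and nothing is said about absent families. The remark on review fits a low rating as well as a missing one. How averages are formed with gaps is commonly left to the analysis plan, which is not shown, so its absence is no finding.

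A reader might infer that the comparison would reverse a real benefit. On the constructed inputs, pooling attended sessions gives 0.426 / 0.70 = 61% for MFG alone and 0.462 / 0.82 = 56% with the app. The same holds among those present at one session. That result comes from weighting families by attendance. One average per family gives 54% in both arms, so the gain is hidden, not reversed. The article does not establish the conditions that a reversal would need. Nor does it show that attendance differs by arm, and attendance is a separate measured domain in which such a gain could be seen.

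What the reply does not remove is that the named method does not fit the data described. That is a choice the article makes, not a detail it leaves open.

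**Conclusion.** The point holds in conditional form. A pre/post MANOVA is a poor choice for ratings from 16 sessions. Entered as one vector, those ratings would leave about 15 of 80 families (independent misses) or about 37 to 49 (clustered misses) at an assumed 90% attendance, tilted towards regular attenders. Analysed by session or by family average, the sample holds, but a gain working through attendance would not show if only attended sessions are rated.

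A reader might also infer that averaging shrinks the comparison to an engaged subset. It does not: any family with one rated session has an average. Its problem is possible bias and unequal precision.

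The attendance rates, the clustering, the 0.6 correlation and the example's inputs are all assumptions. The consequence is limited, because the analysis is secondary and exploratory in a trial declared underpowered. It matters because the effect size is the signal carried into a future trial, and the stated caution covers sample size but not selection.

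**What to change.** 1. Replace the MANOVA with a likelihood-based mixed model on the session ratings, with family as the repeated unit, using every available rating and analysing families as randomised. Report the number with no rating in each arm.
2. Add, as a labelled sensitivity analysis, homework completed over the whole programme per randomised family, with a missed session or unattempted assignment counted as 0. The mixed model alone would not show a gain that works through attendance.
3. Report the number of rated sessions per arm beside the quantity, quality and review results.
4. Extend the caution on the secondary results to selection through missed or unrated sessions.

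The cost is analysis wording and a few table rows. No new data are needed: attendance is already recorded, and the article's status section says the data are still being coded, cleaned and analysed. There are two small downsides. Scoring zero is a convention, hence the sensitivity label, and the mixed model assumes that ratings are missing at random given what was observed.

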##### Current status of the study

Phase I pilot studies have been completed with further refinement to My MFG application being made and refinements to the study protocol. Phase II: small-scale pilot randomised controlled trial was recently completed and study data are being coded, cleaned, and analyzed.

## Discussion

The National Institute of Mental Health [36, 37] in the United States has specifically called for acceleration of research to maximize the potential of current treatments to reduce symptoms and enhance functioning while improving quality of and lowering the cost of care. The mHealth application and methods proposed herein serve as systematic, theory-driven approach to significantly advance understanding of how best to support the homework process—a common element of many evidence-based treatments across various disorders and populations [25]. Ultimately developing methods to support homework implementation should result in greater implementation and generalization of behavioral skills learned during treatment which should maximize the effectiveness of these evidence-based treatments.

Given the prevalence of DBDs and the limited resources available in outpatient mental health clinics serving disadvantaged communities, maximizing the potential effectiveness and efficiency of existing evidence-based treatments for DBDs, such as MFG, is a high public health priority. We hypothesize that My MFG, which is based on a strong theoretical foundations [9, 31–33], employed through mHealth features via smartphones we have successfully utilized in previous work [34, 35] offers an opportunity to significantly improve the effectiveness of MFG. Importantly, the data gathered through the series of pilot studies described herein allow for a preliminary evaluation and development of the My MFG application. Summary statistics data from the RCT study will inform the extent to which the My MFG application results in high levels of quality and quantity in the homework process and allows for identification of specific content, processes, and/or methods employed in My MFG application that do not appear to result in high rates of quality homework process. The secondary analyses, while underpowered, will allow for detection of a possible “signal” that suggests benefit of My MFG relative to MFG alone. Qualitative feedback from consumers and user data from the My MFG application will augment the session-by-session data. Collectively, the multi-method and multi-informant strategy will allow for further refinement of the my MFG application for potential evaluation in a well-powered subsequent RCT. Lastly, the study RCT will allow us to gauge an important aim—the extent to which the study protocol is feasible and whether and what modifications will need to be made prior to a larger scale evaluation.

Utilizing relatively simple mHealth methods to augment the benefits of existing psychosocial treatments should also improve the quality of overall care for families while not significantly increasing the burden of treatment for both families and clinicians. There is significant data demonstrating that the demands of parenting interventions, in terms of amount of time, effort, and resources needed from families to participate in the intervention, are directly related to engagement and dropout from treatment [38]. mHealth offers the opportunity to streamline parenting interventions to be less demanding upon families and thereby increasing the chances that interventions can be more readily implemented, particularly in mental health settings serving families from resource-poor communities. Likewise, interventions can be burdensome for clinicians, resulting in difficulties with overall implementation and sustained use [19, 39]. mHealth methods may offer the promise of replacing effective but time-intensive approaches to supporting homework (e.g., phone call reminders), thereby decreasing the burden of an intervention for clinicians. Ultimately, mHealth methods may prove to be vital to augment evidence-based interventions and increase the chances of successful adoption/implementation of these interventions in clinical practice settings.

## Abbreviations

CD: Conduct disorder
DBDs: Disruptive behavior disorders
MFG: Multiple family group
mHealth: Mobile health
ODD: Oppositional defiant disorder
